## Abstract

**Introduction:**

Although immune checkpoint inhibitors (ICIs) have changed the treatment landscape of advanced non-small cell lung cancer (NSCLC), their low response rates and immune-related adverse reactions (irAEs) remain serious challenges. Traditional Chinese medicine believes that “spleen deficiency” is the core pathogenesis of advanced lung cancer, and its corresponding immune suppression and metabolic disorders may be related to the efficacy of ICIs. This paper aims to explore the clinical application status and potential mechanisms of traditional Chinese medicine combined with ICIs based on the “strengthening the spleen”. Literature analysis shows that traditional Chinese medicines for invigorating spleen have shown positive trends in improving patients ‘quality of life and reducing irAEs. Their mechanism of action may involve pathways such as regulating the “gut-lung axis” and reshaping the tumor immune microenvironment. However, this field still faces challenges such as the lack of high-quality randomized controlled trials, inconsistent dialectical standards, and unclear molecular mechanisms. Accordingly, we designed the present trial to explore the therapeutic efficacy and safety profile of JPGC combined with ICIs in patients with NSCLC.

**Methods/design:**

The evaluation design of the JPGC clinical trial was a randomized, double-blind, placebo-controlled study. The sample size is 56, and there are 28 participants in the test group and control group respectively. The test group received JPGC, and the control group received JPGC placebo. There is a course of treatment every 21 days for a total of 4 courses. The main outcomes include 6-month PFS rate, secondary outcomes include PFS, exploratory study endpoints include TCM syndrome integral, EORTC QLQ-C30, ECOG score, intestinal barrier, intestinal flora, inflammatory cytokines, T cell subsets, etc.

**Discussion:**

We predict that by repairing the intestinal barrier and adjusting the stability of intestinal flora to enhance the efficacy of immunotherapy for non-small cell lung cancer, non-small cell lung cancer patients will improve spleen deficiency and quality of life through JPGC. This study used TCM syndrome analysis, laboratory tests, imaging examinations and other indicators to evaluate the clinical efficacy and safety of JPGC. Fecal metabolomic analyses will be implemented in trial subjects to explore the latent synergistic mechanisms associated with JPGC intervention. This is a traditional Chinese medicine trial to observe and treat advanced NSCLC characterized by spleen deficiency syndrome by directly regulating intestinal flora. If successful, this discovery will have value in antitumor therapies and drug development, especially in the “immune era.”

**Clinical Trial Registration:**

https://itmctr.ccebtcm.org.cn, identifier ITMCTR2025002090.

## Introduction

1

Lung cancer ranks first in the world’s cancer cause (1), of which non-small cell lung cancer (NSCLC) accounts for approximately 85% (2). Immunotherapy with PD-1/PD-L1 inhibitors as the core has been extended from advanced to perioperative periods, bringing long-term survival benefits by reshaping tumor-immune interactions (3), but its clinical limitations are significant: it is difficult to accurately screen beneficiaries, and the suppressed state of the tumor immune microenvironment (TME) and brain metastases limit efficacy (4, 5); immune-related adverse reactions (irAEs) are mainly organ-specific inflammation, and combined treatment adds risks (6, 7); Drug resistance involves multiple mechanisms such as primary, acquired and physical barriers, and some patients even experience hyper progression (8–10). For stage IIIB-IV NSCLC, although ICIs are standard treatment, the single-agent response rate is still limited, and irAEs are common.

Traditional Chinese medicine can increase efficiency, attenuate toxicity, delay drug resistance and improve quality of life (11, 12), It can enhance efficacy by regulating immunity and reshaping TME (13), reduce the incidence of irAEs (14), and use multi-target intervention to delay drug resistance (15). Traditional Chinese medicine regards the “spleen” as the foundation of the day after tomorrow. Patients with advanced lung cancer generally have the pathogenesis of “spleen qi deficiency”, which is manifested by fatigue, poor appetite, and loose stools. “Spleen deficiency” is closely related to low immune function, chronic inflammation and intestinal flora disorders (16–18), which are the key factors affecting the efficacy of ICIs. Jianpi Guchang prescription (The drug composition is detailed in **Table 1**) is a self-made clinical experience prescription based on the theory that “the lung and the large intestine are mutually exterior-interior”. Preliminary research by our research team found that JPGC intervention in chemotherapy patients can effectively resist the increase in intestinal mucosal permeability and intestinal inflammation caused by chemotherapy. Reaction, thereby protecting the intestinal barrier function, enhancing the body’s immunity, and promoting the recovery of intestinal flora diversity after chemotherapy (19, 20). Jianpi Guchang prescription maintains the steady state of intestinal flora and protects the intestinal barrier function by regulating the metabolism of short-chain fatty acids; at the same time, it promotes Foxp3 expression by down-regulating the activity of the PI3K/Akt signaling pathway, and indirectly regulates the tumor immune microenvironment, and ultimately exerts a tumor inhibitory effect (21). In the clinical application of patients with advanced metastatic colorectal cancer, this compound treatment has been shown to extend the median survival time of patients by 5.06 months and significantly improve the quality of life of patients. Therefore, the strategy of combining the principles of strengthening the spleen with ICIs has a solid theoretical basis and transformation potential. We designed this study to focus on the effectiveness and safety of JPGC combined with ICIs in the treatment of non-small cell lung cancer.

**Table 1 T1:** Components of JPGC prescription.

Chinese name	Latin name	Source plant	Dosage (g)
Huang Qi	*Astragalus membranaceus*	The dried roots of Mongolian milkvetch Astragalus membranaceus (Fisch.) Bge. var. mongholicus (Bge.) Hsiao and membranous milkvetch Astragalus membranaceus (Fisch.)	30
Fu Ling	*Wolfiporia cocos*	Dried sclerotium of the polypore fungus Poria cocos (Schw.) Wolf.	10
Bai Zhu	*Atractylodes macrocephala*	Dried rhizome of Atractylodes macrocephala Koidz., a plant of the Asteraceae family	10
Dang Shen	*Codonopsis pilosula*	Dried root of Codonopsis pilosula (Franch.) Nannf., a Campanulaceae plant	10
Tu Fu Ling	*Smilax glabra*	Dried rhizomes of the Liliaceae plant Smilax glabra Roxb	10
Ba Qia	*Smilax china*	Dried rhizome of Smilax china L., a plant of the Liliaceae family	10
Teng Li Gen	*Actinidia arguta*	For the roots of the kiwifruit plant Actinidia chinensis Planch	10
Ba Yue Zha	*Holboellia angustifolia*	Fruit of the Akebia family plant Akebia trifoliata (Thunb) Koidz var. australis (Diels) Rehd. or three-leaf Akebia A. trifoliata (Thunb.) Koidz., five-leaf Akebia A. quinata (Thunb.) Decne	10
Ji Nei Jin	*Galli Gigerii Endothelium Corneum*	The inner wall of the dry gizzard of the domesticated chicken Gallus domesticus Brisson	5

## Methods

2

### Study design

2.1

Guided by the core theories of traditional Chinese medicine that “strengthening the body and treating cancer” and “the lung and the large intestine are mutually exterior-interior”, through Placebo-controlled randomized double-masked clinical investigation, we evaluated the efficacy of integrated traditional Chinese and Western medicine based on “Jianpi Guchang prescription” as the basic prescription in the treatment of spleen deficiency type stage IIIB-IV non-small cell lung cancer, prolonging patients ‘progression-free survival and improving their quality of life, obtaining high-level evidence-based medical evidence, and forming a standardized diagnosis and treatment plan that can be promoted.

### Sample size calculation

2.2

The study estimated the sample size required for this study based on the main efficacy indicators. According to the preliminary clinical treatment results, the effective rate in the traditional Chinese medicine treatment group is 50%, and the effective rate in the control group is 10%. Assuming that the type I error probability of this study is α=0.05, and the power (1-β) = 90%. Therefore, substitute P1 = 50%, P2 = 10%, α=0.05, β=0.1, μ_α/2_ = 1.96, μ_β_=1.282 into the formula and n=23. Based on the above calculation, 23 cases are needed in each group. Taking into account the 20% sample loss rate, 28 cases should be recruited in each group, i.e., n1=n2 = 28, for a total of 56 cases in the two groups.

$$n=\frac{p_{1}\times (1-p_{1})+p_{2}\times (1-p_{2})}{{\left(p_{1}-p_{2}\right)}^{2}}\times {\left(\mu_{\alpha /2}+\mu_{\beta }\right)}^{2}$$

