### Primary outcome

4.1

6-month PFS rate: the proportion of all randomized participants who are free of disease progression (assessed per iRECIST criteria) and free from all-cause death at the 6-month time-point from randomization.

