### Exploratory study endpoints

4.3

Including TCM syndrome integral, EORTC QLQ-C30, ECOG score, intestinal barrier, intestinal flora, inflammatory cytokines, T cell subsets, etc.

TCM syndrome integral: TCM syndrome integral record time refer to evaluation time point in **Table 2**.

TCM Syndrome Points:

The severity of primary symptoms and secondary symptoms was divided into 0, I, II and III according to the single scoring standard of primary symptoms and secondary symptoms. Grade 0: asymptomatic, 0 points; Grade I: mild symptoms, not affecting daily life and work, 1 point; Grade II: moderate symptoms, partially affecting daily life and work, 2 points; Grade III: severe symptoms, affecting daily life, difficult to persist in work, 3 points.

The evaluation of syndrome efficacy includes changes in main symptoms, secondary symptoms, signs, and tongue images. It is calculated using nimodipine method. The efficacy index = [(pre-treatment points subtract post-treatment points)/pre-treatment points]×100%, which is divided into 4 levels: clinical recovery, effective, and ineffective.

1. Clinical recovery: The main symptoms, secondary symptoms, and signs disappeared or basically disappeared, the tongue picture basically returned to normal, and the efficacy index was ≥95%;2. Effective effect: The main symptoms, secondary symptoms, signs, and tongue symptoms have been significantly improved, with 70%≤ efficacy index <95%;3. Effective: The main symptoms, secondary symptoms, signs, and tongue symptoms have improved, 30%≤ efficacy index<70%;4. Ineffectiveness: The main symptoms, secondary symptoms, signs, and tongue manifestations have not been significantly improved or even worsened, and the efficacy index is<30%.

Quality of life QOL score and weight monitoring: application of EORTC QLQ-C30 scale.

A standardized PRO management and compliance monitoring plan is preset for the study: questionnaires are filled out independently at baseline, every 2 treatment cycles, and on site at the end of treatment. The investigators only provide process answer questions and do not induce answers. The questionnaire completion rate, missing item rate and compliance were monitored throughout the process; cases with low compliance were recorded, and the robustness of the results was verified through sensitivity analysis.

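### The 90% power in section 2.2 rests on an undefined effective rate that is never tied to the 6-month PFS rate, the primary endpoint

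*Protocol article*

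**What the plan says.** Section 2.2 opens by tying the calculation to the main outcome: "The study estimated the sample size required for this study based on the main efficacy indicators". Two rates then serve as inputs: "the effective rate in the traditional Chinese medicine treatment group is 50%, and the effective rate in the control group is 10" per cent. The only origin offered for them is the phrase "According to the preliminary clinical treatment results". The error rates are given as "the type I error probability of this study is α=0.05, and the power (1-β) = 90" per cent, and the substitution is "α=0.05, β=0.1, μ_α/2_ = 1.96, μ_β_=1.282 into the formula and n=23". Then: "Taking into account the 20% sample loss rate, 28 cases should be recruited in each group", for 56 in total.

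Section 4.1 defines the primary outcome, the 6-month PFS rate, as "the proportion of all randomized participants who are free of disease progression" (by iRECIST) and alive at 6 months from randomization.

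The article uses the word effective as an outcome grade only in section 4.3. There the TCM syndrome efficacy index, an exploratory endpoint, is one "which is divided into 4 levels: clinical recovery, effective, and ineffective". No section gives an expected 6-month PFS rate for either arm.

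**The concern.** A power statement is a statement about a particular endpoint. Section 2.2 prints a complete calculation but leaves the quantity behind p1 and p2 undefined: no time point, no population, no definition of success. It appeals to the main efficacy indicators without naming them, and the label on the rates matches nothing in the definition of the primary outcome.

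Both readings cause difficulty. If the rates describe a syndrome or other response, the trial was sized on a different endpoint and its power for 6-month PFS has not been stated. If they describe 6-month PFS, they assume a very poor control arm and a very large add-on effect over the background immunotherapy, with or without chemotherapy, described in section 3.8. The earlier work summarised in the Introduction concerns chemotherapy patients and metastatic colorectal cancer and reports no PFS data in NSCLC.

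What is at stake is how the result is read. A non-significant comparison from a trial said to have 90% power will be taken as evidence against efficacy, although a trial of this size may have little chance of detecting a moderate benefit.

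**Working it through.** **Inputs from the article.** Section 2.2: p1 = 0.50, p2 = 0.10, z = 1.96 (two-sided 0.05), z = 1.282 (90% power), 20% loss, 28 per group. Section 3.7: 1:1 allocation. Section 4.1: all randomized participants count. Section 4.10: chi-square test for count data.

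**1. Reproduce the plan's figure.**

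n = [0.5 × 0.5 + 0.1 × 0.9] / 0.4² × (1.96 + 1.282)² = 0.34 / 0.16 × 10.51 = 22.33, so 23 per group.

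Loss: 22.33 / (1 − 0.20) = 27.92, so 28 per group and 56 in total. Both stated figures reproduce.

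**2. Read the inputs as 6-month PFS rates (constant hazard assumed).**

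- Control median: 6 × ln 2 / ln 10 = 1.8 months.
- JPGC median: 6.0 months, since 50% are event-free at 6 months.
- Hazard ratio: ln 0.5 / ln 0.1 = 0.30.

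On this reading half the control arm would progress or die within about 8 weeks.

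**3. Power of the 56 patients for 6-month PFS.** The article gives no control rate, so 30%, 40% and 50% are assumptions. The method is full enumeration of two binomials with 28 per arm, two-sided Pearson chi-square at 0.05 without continuity correction, and no loss.

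| Control 6-month PFS (assumed) | +20 points | +30 points | +40 points | JPGC rate needed for 90% power |
|---|---|---|---|---|
| 30% | 33% | 61% | 86% | about 72.5% |
| 40% | 31% | 61% | 88% | about 81% |
| 50% | 33% | 67% | 94% | about 88% |

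The gain needed for 90% power is therefore about 42.5, 41 and 38 points respectively.

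**4. Same method at the plan's own rates.** With 50% versus 10% and 28 per arm, exact Pearson power is 93.6%. The 90% claim is attainable for those rates. What is missing is the link from those rates to the primary endpoint.

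**The case against.** The strongest reply is that section 2.2 says it rests on the main efficacy indicators, and the Abstract lists the 6-month PFS rate as the main outcome. The odd label may be loose wording or translation. Section 4.3 speaks of an efficacy index and grades and never uses the term effective rate. This stands to the extent that the rate cannot be shown to be something other than 6-month PFS. It remains undefined, and the PFS reading needs a source that the article does not identify.

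A second reply is that a journal article condenses, and the full protocol may describe the preliminary data. That is fair for details of the source. It does not cover the meaning of p1 and p2 when the formula, inputs and power are all printed.

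Third, a control median of 1.8 months does not contradict the inclusion rule of at least 3 months' expected survival, because survival is not PFS, and the figure depends on constant hazards. This is accepted. The implied values need justification but are not impossible. The 30–50% control rates are likewise assumptions.

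A reader might also draw three stronger conclusions that the article does not support:

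- **That the loss allowance is miscalculated.** Rounding first gives 23 / 0.8 = 28.75, so 29, and 23 × 1.2 = 27.6 also rounds up to 28. But 22.33 / 0.8 = 27.92 gives the stated 28 by the correct method, and the article does not show which route was taken.
- **That the unpooled formula is an error because a pooled-variance formula gives 26 per group.** This is a choice between accepted formulas.
- **That true power at 50% versus 10% is only 86%.** That needs a full 20% loss, leaving 22 per arm, with those patients dropped. Section 4.1 counts everyone randomized, which gives 93.6%.

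**Conclusion.** The point holds in this form: the 90% power is not supported, by anything the article states, as the power for the 6-month PFS rate. It would go too far to say that the calculation certainly uses another endpoint or has no basis at all, because the reference to the main efficacy indicators leaves the PFS reading open.

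The consequence is substantial under the assumed control rates of 30–50% with all 28 per arm analysed. Power is about one third for a 20-point gain and about 61–67% for a 30-point gain, and it reaches 90% only for gains of roughly 38 to 42.5 points. If the control rate really were 10%, the design would be adequate for a rise to 50%, but that means accepting a control median near 1.8 months and a hazard ratio near 0.30 under constant hazards. No corrected sample size can be computed from the article, since it supplies no 6-month PFS rate.

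**What to change.** In section 2.2, state p1 and p2 as 6-month PFS rates that match section 4.1 (from randomization, iRECIST progression or death from any cause), give the population and source of each, and recompute power on them.

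If no such rates exist, keep N = 56 and replace the 90% claim with the power, or the detectable difference, over a stated range of control rates, as in the table above. Name the test used for the power figures.

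The cost is protocol wording, with no extra patients. The downside is that the stated power becomes less favourable. Section 2.3 says recruitment is ongoing and section 4.6 plans an interim analysis that can stop the trial for benefit, so the change should be made and dated before that analysis and before unblinding.

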### Recruitment

2.3

The 56 cases in this study were all from advanced lung cancer patients who received immunotherapy at Shanghai TCM-Intergrated Hospital Shanghai University of Traditional Chinese Medicine. All subjects participating in this trial shall provide written informed consent prior to enrollment. The trial workflow is illustrated in **Figure 1**. Subject recruitment remains ongoing as of the date of submission. The first subject was enrolled on June 25, 2026, and the trial is projected to conclude in October 2027.

**Figure 1 f1:**
[figure not shown]
Participant flowchart.

## Participants selection

3

### Diagnostic criteria

3.1

#### Modern medical diagnosis

3.1.1

Refer to the “Guidelines for the Diagnosis and Treatment of Non-Small Cell Lung Cancer” formulated by CSCO in 2024; TNM pathological staging (pTNM) adopts the 8th edition of AJCC/UICC.

#### TCM diagnosis

3.1.2

Two deputy chief physicians independently conducted syndrome differentiation according to the “Clinical Research Guidelines for the Treatment of Spleen Syndrome with Traditional Chinese Medicine” to determine whether the diagnostic criteria for spleen deficiency syndrome were met. Clinical manifestations must have more than 2 or at least 2 spleen main symptoms, or 1 spleen main syndrome and 2 spleen secondary syndromes. When the conclusions of the two are inconsistent, the final syndrome results will be reviewed by a more senior chief physician of traditional Chinese medicine.

##### Main symptoms

3.1.2.1

① Reduced appetite or poor appetite; ② abnormal stool (loose, rotten, dry first and then thin, etc.); ③ abdominal distension after eating or abdominal distension in the afternoon.

##### Secondary symptoms

3.1.2.2

④ The mouth is light but not thirsty; likes hot drinks; ⑤ The mouth is full of clear saliva; ⑥ Continuous abdominal pain, or likes warm and pressed pressure, or reduces when you get food, or it occurs when you feel tired; ⑦ Nausea and vomiting; ⑧ Stomachiness; ⑨ Bowersounds; ⑩ Weight loss or puffy; pale complexion; pale lips; Shortness of breath; Weak bowel movement; leucorrhoea; clear and thin urine; Excessive phlegm; Insomnia and insomnia.

Tongue pulse: pale tongue, teeth marks on the sides, white and thick greasy coating; pulse number.

Anyone who meets any 2 of the above main symptoms ① to ③, or any 1 of ① to ③ plus any 2 of ④ to, and satisfies the spleen deficiency tongue pulse, can be identified as spleen deficiency syndrome.

### Inclusion criteria

3.2

A patient with pathologically confirmed non-small cell lung cancer and stage IIIB-IV who did not meet the surgical indications according to UICC version 8;It conforms to traditional Chinese medicine syndrome differentiation and is classified as spleen deficiency syndrome;Willing to receive immunotherapy;No antibiotics, systemic corticosteroids (or prednisone doses less than 10mg/day) or other immunosuppressants were used within 1 month before enrollment;No inflammatory bowel disease, radiation enteritis, rheumatic immunity and other diseases;No other serious complications;Aged between 18 and 80 years inclusive, male or female subjects;ECOG ≤ 2, estimated survival time ≥3 months;Baseline laboratory tests met the following criteria: neutrophils ≥1.5×10^9/L, platelets ≥80×10^9/L, hemoglobin ≥ 90 g/L, Serum alanine aminotransferase (ALT) and aspartate aminotransferase (AST) ≤2.5 times the upper limit of normal (if AST is allowed when liver metastasis is present, ALT ≤ 5 times the upper limit of normal), bilirubin ≤1.5 times the upper limit of normal, and creatinine ≤1.5 times the upper limit of norma, serum creatinine ≤ULN to 1.5 times, INR ≤ 1.5 or prothrombin time (PT) extension no more than 3 seconds in normal control.

### Exclusion criteria

3.3

Those with severe primary diseases such as severe cardiovascular and cerebrovascular diseases, as well as mental illness;Poor compliance and incomplete data during clinical research;The diagnosis is unclear;Subjects who cannot perform the provisions of this experimental protocol;Subjects whose observation items are incomplete and cannot evaluate the test effect and side effects;Those who have participated in other clinical trials in the past 3 months;Patients who are pregnant or breastfeeding;Those who have received other immune-related therapies or other therapies that may affect immune function;During the medication process, those who suffer from other diseases due to non-drug factors and cannot continue to complete treatment.

